### Sample size

A sample size of 60 eligible young Muslim women from Birmingham and London (30 per site and 30 per arm) has been selected to enable 24 participants per arm at the final follow-up point, allowing for an estimated loss to follow-up of up to 20% (co-applicant GM’s study unpublished [58, 59]. This sample size allows for at least one IM-Adapted intervention group to be completed at each of the two study sites, giving six groups in total (3 intervention; 3 control). Each group is required to have 10 participants to ensure that at least 8 participants are present at any given session (allowing for 20% no show/drop out). As this is a feasibility study, the sample size is not powered to evaluate the efficacy of the intervention. A sample size of 60 participants will allow estimation of the completion rate to within a pre-specified level of precision of ± 10% assuming it is 90%, or ± 13% if it is 80%. We are confident that these are appropriate estimates and represent values that would allow progression to a full trial. The sample size is also in line with those for feasibility studies audited in the UK [60].

### Recruitment

Young women will be informed about the study through mosques and community groups supporting recruitment for the study and through IM’s usual referral processes, study website, and social media. Individuals will be directed to complete the online self-referral form held on the IM website.

Study staff at IM will review incoming referrals to their services, via their usual online form, to identify those who meet the initial eligibility criteria check (i.e. are the right age, gender and have reported low mood/depression scoring 5–14 on the PHQ-9). Those meeting the initial eligibility check will be contacted to introduce the study and set up a consultation via telephone or video call. This includes a standard risk assessment undertaken by IM staff to finalise eligibility for participation in the study.

Those who are ineligible based on risk or other eligibility criteria or do not wish to participate in the study will be offered the usual support provided by IM as appropriate. These individuals will be offered the option to give reasons for why they do not wish to participate in the study, but this question will be optional to avoid apparent coercion.

Those who meet all eligibility criteria for the study and would like to take part will be sent the link to the online (via REDCap) informed consent form.

## Methods: assignment of interventions

### Allocation

Participants will be recruited and placed sequentially into a group at each site; once the group at the site has reached 10 participants, the group will be allocated. The allocated treatment for a group will be automatically generated via the study database. Stratification will be by study site (Birmingham or London) with a block size of 2. The groups will be allocated by a process embedded in the web-based data management system REDCap [61, 62] managed by the University of Hertfordshire Clinical Trials Support Network (UHCTSN) ensuring allocation concealment. When a group is randomised, an email will be sent to the principal investigator (PI) and the Trial Manager, who will communicate with the Therapist and MHSW to set up the appropriate group sessions.

Due to the nature of the intervention, allocation blinding is not possible. Where possible, both supporting staff will be blinded during data collection and statistical analyses will be blinded. 

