### Trial design

A two-arm cluster randomised controlled feasibility trial delivered in groups in two locations (Birmingham and London). Clusters will each comprise 8–10 young Muslim women, with three groups at each site. This trial incorporates embedded mixed methods process evaluation.

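### Blocks of 2 within site cannot balance three groups per site, so the stated 3:3 groups and 30 women per arm arise only half the time

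*Protocol article*

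**What the plan says.** Three sections of the protocol article bear on this point.

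- **Trial design** describes a cluster trial in Birmingham and London "with three groups at each site", each group having 8 to 10 women.
- **Sample size** sets 60 women, "30 per site and 30 per arm", a number that "has been selected to enable 24 participants per arm at the final follow-up point" after up to 20% loss. It promises "at least one IM-Adapted intervention group to be completed at each of the two study sites", "giving six groups in total (3 intervention; 3 control"), with 10 women required in each group.
- **Allocation** fills groups one after another at each site and allocates each when it reaches 10 women. The rule is: "Stratification will be by study site (Birmingham or London) with a block size of 2".

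No section links the allocation lists of the two sites or constrains the overall split between arms.

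**The concern.** A permuted block of 2 balances the arms within a stratum only when the stratum holds an even number of units. Here the stratum is a site and the unit is a group, and each site has three. The first two groups at a site take one arm each. The third starts a new block whose second place is never used. With nothing tying Birmingham's third group to London's, both can fall in the same arm.

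The Sample size section gives 3:3, 30 per arm and 24 per arm as features of the design, not as averages over possible randomisations. If the third groups coincide, one arm has two groups and a third fewer women than stated.

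Per-arm numbers are used. Statistical methods reports stage proportions with confidence intervals by study arm, and outcome summaries and adverse events by arm. Two of the Progression criteria compare the arms, on effectiveness and on adverse events. The process evaluation aims to interview about 12 women from each arm, which would be 12 of 20 randomised women in the smaller arm instead of 12 of 30.

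**Working it through.** **Inputs.** Two sites, three groups per site (Trial design). Ten women per group, 30 per arm, 24 per arm at final follow-up, 20% loss (Sample size). Blocks of 2 within site (Allocation). Allocation at 1:1 is implied by the block size and the 3:3 plan.

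**1. The plan's own figures.** 24 / (1 − 0.20) = 30 per arm; 3 groups × 10 = 30; 6 groups × 10 = 60. The stated sizes agree with one another. The question is whether the allocation rule delivers them.

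**2. Allocations under the written rule.** Each block is intervention–control or control–intervention with equal probability. Three groups at a site use the first block and half of the second, so each site has 2 × 2 = 4 equally likely sequences, and two sites have 4 × 4 = 16. Each site's first block contributes one intervention group, and each third group is an intervention group with probability 1/2. So:

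number of intervention groups = 2 + Binomial(2, 1/2)

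| Groups, intervention : control | Sequences of 16 | Probability | Women at entry | After 20% loss |
|---|---|---|---|---|
| 3 : 3 | 8 | 1/2 | 30 v 30 | 24 v 24 |
| 4 : 2 | 4 | 1/4 | 40 v 20 | 32 v 16 |
| 2 : 4 | 4 | 1/4 | 20 v 40 | 16 v 32 |

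If groups hold 8 or 9 women, which Trial design allows, the two-group arm has 16 or 18 at entry, with the same probabilities.

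For comparison, blocks of 2 over all six groups without site strata would give 3:3 every time. The imbalance comes from combining site strata with an odd number of groups.

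**3. Precision within an arm.** Half-width = 1.96 × √(p(1 − p)/n), with p = 0.80 and clustering ignored:

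- Entry, planned: 1.96 × √(0.16/30) = 0.143
- Entry, smaller arm: 1.96 × √(0.16/20) = 0.175
- Entry, larger arm: 1.96 × √(0.16/40) = 0.124
- Follow-up, planned: 1.96 × √(0.16/24) = 0.160
- Follow-up, smaller arm: 1.96 × √(0.16/16) = 0.196

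One arm loses precision and the other gains some.

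**4. Difference between arms.** Ratio of standard errors = √(1/40 + 1/20) / √(1/30 + 1/30) = √0.0750 / √0.0667 = 1.06, a rise of about 6%.

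**5. What does not change.** The first block at each site always contains one intervention group, so every one of the 16 sequences keeps at least one IM-Adapted group per site. The ±10% and ±13% completion-rate precision in Sample size is stated for all 60 women, so the split does not enter it.

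**The case against.** The strongest reply is that little depends on an exact 3:3 split. The only stated precision target uses the whole sample. The numeric traffic lights in Progression criteria (outcome completion, session attendance, resource-use data) set no per-arm thresholds. Statistical methods calls the analysis largely descriptive and rules out formal hypothesis tests, and Sample size says that the trial is not powered for efficacy. The IM-Adapted arm, whose delivery is the main feasibility question, falls to two groups in only a quarter of sequences, and in another quarter it gains a fourth. All of this stands and limits the harm.

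A reader might infer that the precision target or a progression threshold fails, or that a site could end without the intervention. The documents support neither, for the reasons just given and in step 5 of the working. A reader might also stress that between-group variation in a two-group arm has a single degree of freedom. No such variance analysis is described, and the intended three groups would give only two degrees of freedom.

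It can also be said that this is a condensed article and that the full protocol may constrain the REDCap list further. That is possible. But the article does not simply leave the detail out: it states a rule and states numbers that the rule does not guarantee. The contradiction therefore stands on the text shown.

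**Conclusion.** The allocation rule and the stated sizes conflict. With probability 1/2 the trial gets its 3:3 groups and 30 (then 24) women per arm. With probability 1/2 it gets 40 v 20 at entry and 32 v 16 at follow-up, and the smaller arm is one third below plan. The cost is a wider interval in that arm (±17.5 instead of ±14.3 points at entry, ±19.6 instead of ±16.0 at follow-up, for an 80% rate) and a standard error for arm differences about 6% larger.

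This is a moderate inconsistency, not a critical one. The result assumes 1:1 blocks, independent lists at the two sites, exactly three groups per site, ten women per group and 20% loss in each arm. The half-widths use the normal approximation and ignore clustering.

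**What to change.** For groups not yet allocated, use an allocation list constrained to 3:3 overall with both arms at each site. Two different schemes achieve this:

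- **Pair the third groups.** Keep the block of 2 for groups 1 and 2 at each site, and make the two third groups one cross-site block of 2. This gives 2 × 2 × 2 = 8 sequences.
- **Draw from all balanced sequences.** Of the 20 ways to place three intervention groups among six, drop the two that give a site only one arm, and draw at random from the remaining 18. This abandons the within-site block of 2.

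If some groups are already allocated, restrict the draw to sequences consistent with them.

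The cost is a revised REDCap allocation table and a short change to Allocation, with no extra women. There is one small downside: the last group's arm becomes predictable from the earlier ones. Under the pairing scheme, predictable groups rise from two of six (the second at each site) to three of six. This matters because allocation is unblinded and the charity's staff screen women and judge eligibility before their group is allocated. The list and the constraint should therefore be withheld from staff who screen and enrol.

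The article reports the trial as recruiting. If allocations already made rule out 3:3, amend Sample size to say that 3:3 and 30 (24) per arm are expected values, and give the 40 v 20 (32 v 16) case or the actual split.

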### Eligibility criteria

Individuals are eligible for inclusion if they are a Muslim woman aged 18 to 24 years, self-diagnosed or referred from another source with low mood or mild depression and scoring between 5 and 14 on the Patient Health Questionnaire 9 scale (PHQ-9) [48], who are willing to take part in the study, consent to participate, and are able to read and understand English.

Individuals will be excluded from the study if they do not meet the above eligibility criteria and are considered unsuitable based on the professional opinion of the IM’s mental health professionals eligibility screening and risk assessment (e.g. presenting significant risk) or their current treatment or co-morbid conditions present contraindications to engaging in the trial (e.g. severe chronic pain).

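### With sequential groups and a fixed block of 2 in an open-label trial, the second group's arm at each site can be deduced while it recruits, so the concealment claim does not hold for those groups

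*Protocol article*

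**What the plan says.** The Trial design section plans two sites, "with three groups at each site", and the Sample size section describes this as "giving six groups in total (3 intervention; 3 control").

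The Allocation section sets the order of events: "Participants will be recruited and placed sequentially into a group at each site", and "once the group at the site has reached 10 participants, the group will be allocated". It gives the restriction as follows: "Stratification will be by study site (Birmingham or London) with a block size of 2". It describes the web-based process as "ensuring allocation concealment". It also states that the arms cannot be blinded, and that each result is emailed to the principal investigator and the Trial Manager, who inform the therapist and the support worker.

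On who enrols, the Recruitment section says: "Study staff at IM will review incoming referrals to their services". The charity's staff then contact the women, introduce the study and complete the risk assessment that settles eligibility. Under Eligibility criteria, a woman may be excluded if she is "considered unsuitable based on the professional opinion of the" charity's mental health professionals. The Study setting and control arm sections show that the same charity delivers both arms. The Trial status section says that recruitment is under way.

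**The concern.** A central web system conceals the next allocation only if that allocation is still uncertain. With a block of 2, the second group at a site must receive the arm that the first did not. The first group's arm is open once its sessions are arranged, and the block size is in print during recruitment. The second group fills after that point, one woman at a time, through a process that leaves room for judgement about suitability.

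If the people who screen can work out the arm, they may differ, knowingly or not, in whom they approach, how they present the study and whom they judge suitable. The second groups could then differ by arm for reasons unrelated to the intervention. That would affect the outcome and stage-of-study proportions that the Statistical methods section reports by arm. It would also affect the criteria that the intervention should show no sign of being less effective than usual care or of raising adverse events. A feasibility trial is also where the enrolment and randomisation procedure for the main trial gets its test.

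**Working it through.** **Inputs.** Two sites and three groups per site (Trial design); 10 women per group, 60 in total, 24 per arm wanted at final follow-up, 20% loss (Sample size); block of 2 within site, groups filled in sequence and allocated at 10 (Allocation).

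**The plan's own figure.** 24 / (1 − 0.20) = 30 per arm, so 60 in total; and 2 sites × 3 groups × 10 = 60. The stated sample size is reproduced.

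**Probability of each arm, given the allocations already made at that site.**

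- Group 1: 1/2 for each arm.
- Group 2: probability 1 for the arm opposite to group 1, because it closes the block.
- Group 3: 1/2 for each arm, because it opens a new block.

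**Determined groups.** One per site × 2 sites = 2 of 6 groups. In women: 2 × 10 = 20 of 60 = 33%. The share does not depend on group size: with 8 per group it is 16 of 48, again 33%.

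**Best-guess rate.** Someone who always guesses the likelier arm is right for 2 × (0.5 + 1 + 0.5) = 4.00 of 6 groups on average. Chance gives 6 × 0.5 = 3.00.

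**Balance under the same scheme.** After two groups each site stands at 1:1. The overall split is 3:3 only if the two third groups, drawn independently, go to different arms: probability 0.50. The split is 4:2 or 2:4 with probability 0.25 each.

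**Cross-site pairs as an alternative.** When both sites have filled their k-th group, one goes to each arm in a single step. There are 2³ = 8 sequences of three pairs. Removing the two in which a site gets the same arm throughout leaves six.

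- Pair 1: likelier arm has probability 1/2.
- Pair 2: the reverse of pair 1 in 2 of the 3 remaining sequences, so 2/3.
- Pair 3: determined if pairs 1 and 2 agree (probability 1/3), otherwise 1/2. The best guess is right with probability 1/3 × 1 + 2/3 × 1/2 = 2/3.

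Determined groups: 2 × 1/3 = 0.67 of 6 on average. Correct best guesses: 2 × (1/2 + 2/3 + 2/3) = 3.67 of 6. The split is always 3:3.

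| Scheme | Fully determined groups | Correct best guesses | 3:3 split |
|---|---|---|---|
| Block of 2 within site (as planned) | 2.00 of 6 | 4.00 of 6 | probability 0.50 |
| Cross-site pairs, six sequences | 0.67 of 6 | 3.67 of 6 | certain |

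**The case against.** Several points on the other side have force.

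- **Knowledge is not documented.** A reader might infer that the charity's screeners know the arm of every woman in the second groups. The article does not say so. It sends each allocation to the principal investigator, the Trial Manager, the therapist and the support worker, and it does not say that these people also screen. Nor does it say that screeners are kept unaware. This stands: 20 of 60 is an upper bound. Some women placed in group 2 may also have been screened or approached before group 1 was allocated, since the article fixes the order of placement, not of first contact.
- **Steering is limited.** Each group is complete and consented before its allocation is issued, the initial check uses fixed criteria (age, gender, PHQ-9 range), and women are placed in order. A woman held back from group 2 would go to group 3, whose arm is even odds. This stands, but it does not prevent differential exclusion from group 2.
- **The effect is narrower than it may seem.** A reader might infer that the feasibility outcomes as a whole are biased. The numerical thresholds under Progression criteria (completion, attendance, resource-use data, share of eligible women recruited) are not stated as comparisons between arms, and no hypothesis test is planned. This stands. What remains exposed is the by-arm description and the two criteria that compare the arms.
- **A larger share might be inferred.** If a 3:3 split were enforced, the last group would also be determined, giving 3 of 6. The article states 3:3 as the plan but gives no mechanism that enforces it, so the count stays at 2.

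None of this restores concealment for the second groups. It limits the consequences.

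**Conclusion.** The point holds as a wrong statement of a design property. Central allocation conceals the arm of the first and third groups at each site. It does not conceal the second, which the design fixes as soon as the first is known. Up to 2 of 6 groups, or 20 of 60 women (33%), are enrolled while their arm can be deduced.

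This rests on the scheme as published: sequential filling, allocation at 10, fixed blocks of 2 within site, three groups per site and no further rule forcing 3:3. For the bias to arise, someone involved in enrolment must also know the first group's arm. That is plausible within one charity that both enrols and delivers, but it is not stated. The documents support no estimate of the size or direction of any bias. A correction of the claim and of the reporting is warranted. The documents do not make a redesign necessary.

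**What to change.** 1. In the Allocation section, restrict the concealment claim to first and third groups, and say that the second group's arm can be deduced from the first. If 3:3 is in fact enforced, say so and add the last group to the exception.
2. Report referrals screened, refusals, exclusions on professional opinion and baseline characteristics by group order and arm, so that a reader can see whether second groups were enrolled differently.

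Both cost almost nothing: a wording change and extra rows or columns in descriptive tables, using screening and baseline records that the trial already plans to keep.

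3. As an option for groups not yet allocated, the sponsor may consider cross-site pairs drawn in one step from the six sequences that give each site both arms. This lowers fully determined groups from 2.00 to 0.67 of 6 on average and guarantees 3:3. The gain is modest, since best guesses still average 3.67 of 6, against 4.00 now and 3.00 by chance. It needs a change in REDCap, and the faster site would have to wait for the slower one. That conflicts with the Interventions section, under which a group is randomised once its own site has enough women, and the delay could increase dropout, which the trial sets out to measure. As recruitment is under way, it may no longer be fully usable.

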## Methods: data collection, management, and analysis

### Data collection methods

Screening data will be collected from the IM database resulting from self-referrals. Participant data will only be entered directly into the study database from the time of informed consent. Data collection, data entry, and any queries will be managed in line with the UHCTSN and trial-specific data management processes.

#### Baseline and follow-up

Participants will be followed up at 6 weeks and 24 weeks. They will receive a link by email to complete outcome measures as online questionnaires on their own devices. An option of telephone data collection will be offered to those participants who would prefer it. To maximise engagement, reminders will be sent via email to those who have not completed the questionnaires and followed up by phone call when necessary; participants will be verbally reminded during the first and last session of when to expect the link to complete measures, and an option of telephone data collection will be offered to those participants who would prefer it.

Attendance, adherence and adverse event data will also be entered into the study database by IM staff and reviewed by the Trial Manager and Chief Investigator (CI) where required. Participants are able to withdraw at any point after enrolling in the study; however, any data collected up to that point will be kept as detailed in the participant information sheet.

#### Outcome measures

Psychological measures.Patient Health Questionnaire-9 (PHQ-9) [48]: a 9-item measure which assesses self-reported severity of depression.Generalized Anxiety Disorder (GAD-7) [63]: a 7-item measure which assesses self-report anxiety.The Warwick-Edinburgh Mental Wellbeing Scale (WEMWBS) [64]: a 14-item measure with 5 response categories which enables the measuring of mental wellbeing.Brief Religious Coping Measure (R-COPE) [54] adapted for a previous trial [65] to include additional questions from Kahn and Watson [55].Direct Measure of Loneliness [66].

Additional measures for use in the economic evaluation:EQ-5D-5L: [67] a five-item measure to assess Health-Related Quality of Life (HRQoL) [68].EuroQol Visual Analogue System (EQ-VAS); a visual analogue scale to assess health status on a scale of zero to 100 to measure health status [67].Modified Client Service Receipt Inventory (CSRI) [68]: a widely used instrument to collect information on services and support used by study participants.

#### Progression criteria

The following criteria have been developed to determine whether funding for a definitive trial will be sought, including items relating to recruitment, retention, adherence, and completion. This progression criteria follow a set of stop–go criteria (based on traffic light colours for the measures, where appropriate). Where traffic lights are used, green = progression (subject to a successful new funding application), amber = modifications and improvements required before progressing, and red = no progression to a future trial. For the non-traffic light measures listed below, a decision will be made based on the information available.Completion of key outcome measures (% of mental health and well-being measures completed):◦ Green: > = 80%◦ Amber: 51–79%◦ Red < = 50%.Participant engagement and attendance (% of planned sessions attended):◦ Green: > = 67%◦ Amber: 51 to 66%◦ Red: < = 50%Successful collection of resource use data (% of participants providing resource use data):◦ Green: > = 80%◦ Amber: 70–79%◦ Red: < 70%Adequate acceptability of interventions to young Muslim women.Professionals and support workers are willing to deliver sessions and encourage participant engagement.Sufficient referrals (with sufficiency based on the sample size required for a definitive trial, we will calculate from this feasibility study) received from various organisations for young people to participate in the trial.Recruitment is such that > = 10% of eligible screened participants are recruited.Appropriate outcomes measures are identified, including one potential primary outcome (> 75% of minimum important difference).Based on the estimated sample size, a necessary number of additional sites is identified for a definitive trial. No indication that the intervention is significantly less effective than usual care.No indication that the intervention has significantly increased the risk of adverse events compared to the control condition.

